### Left ventricular end-diastolic volume

The standard deviation of the difference of LV end-diastolic volume measurements has previously been reported as 23.8 ml [55]. Following CRT reductions in LV end-diastolic volumes are variable but of the order of 25 ml [56] On this basis 338 patients provides >99% power to detect a margin of equivalence of 12.5 ml (50% of clinically significant difference), and permits a difference of 7.4 ml to be detected with 90% power at a significance level of 5%.

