### Sample size calculations

All sample size calculations were based on paired t-tests comparing outcomes for echocardiographic optimization versus haemodynamic optimization.

The reproducibility of peak VO_2_ in heart failure patients between two separate visits using a smoothed modified Bruce protocol on a standard treadmill is 2.4 ml/kg/min, expressed as standard deviation of difference between two independent measurements [48]. Implantation of a CRT pacemaker results in a 0.5-2.5 (mean 1.5) ml/kg/min increase in peak VO_2_[8,9,49-53]. Simply implanting a CRT device yields a haemodynamic improvement of 5–6 mmHg of systolic blood pressure [11,12]. Optimizing the settings after implantation appears in preliminary work to add a further 3-6 mmHg increase in pressure, [1] i.e. between 50-100% of the effect of CRT.

The study sample size was chosen to have 90% power to detect a margin of equivalence of 0.75 ml/kg/min at the 5% significance level. This is the smallest difference between the treatment mean and the reference mean that still results in the conclusion of non-inferiority and corresponds to half the expected clinically meaningful difference as advocated by Jones *et al*. [54] using a one sided *t*-test of equivalence in means. On this basis 338 patients (N1 = 177/N2 = 177) are required. Mean mortality and dropout in similar populations over a 12-month period has been observed to be between 10% and 15%. In order to accommodate possible losses to follow-up as high as this, the target enrolment is 400 patients.

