### Quality of life and NT-pro BNP

For SF-36, the standard deviation of the difference of scores has previously been reported to be 26 [17]. Previous studies of CRT have reported improvements of ~17. With 338 patients we have 92% power to detect a margin of equivalence of 8.5 at a significance level of 5%. For the Minnesota questionnaire, mild improvements in QoL are represented by a change of 12 with a typical standard deviation of 15 [48]. With 338 patients we would be able to easily detect a mild improvement of this magnitude (>99% power) and have 90% power to detect an equivalence limit of 4 points in the Minnesota score.

For NT-proBNP, CARE-HF reported median reductions of 656 pg/ml in NT-pro BNP (adjusted for change in control group) [10]. The within subject coefficient of variation (σ_w_/mean) in log NT-proBNP levels in people with chronic heart failure over 12 months has been reported to be ~10%, i.e. around 190 pg/ml [57]. Assuming a log normal distribution of NT-proBNP, with 338 patients we will be able to easily detect an equivalence limit of half the clinically reported difference with >99% power at 5% significance level and have 90% power to detect an equivalence limit of 0.062 log units (i.e. a fall in baseline NT-pro BNP from 1900 pg/ml to 1647 pg/ml) at a 5% significance level.

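### The LVEDV limit of 7.4 ml and the SF-36 power of 92% are two-group results with 177 per arm, not paired results for 338 patients; the Minnesota limit cannot be reproduced as described

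*Protocol article*

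**What the plan says.** The section Sample size calculations fixes the method for everything that follows: "All sample size calculations were based on paired t-tests comparing outcomes for echocardiographic optimization versus haemodynamic optimization". For peak VO2 it describes a one-sided test, asks for "90% power to detect a margin of equivalence of 0.75 ml/kg/min at the 5% significance level", and concludes: "On this basis 338 patients (N1 = 177/N2 = 177) are required". The two bracketed numbers add to 354, not 338.

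Three secondary-endpoint figures are then attributed to 338 patients:

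- **LVEDV** (section Left ventricular end-diastolic volume). The SD is 23.8 ml and is described as that of the difference. The sample size "permits a difference of 7.4 ml to be detected with 90% power at a significance level of 5" per cent.
- **SF-36** (section Quality of life and NT-pro BNP). The SD is 26, again described as that of the difference. "With 338 patients we have 92% power to detect a margin of equivalence of 8.5 at a significance level of 5" per cent.
- **Minnesota score** (same section). The SD is 15 and is called only typical, without saying whether it belongs to a difference or to a single score. The trial is said to "have 90% power to detect an equivalence limit of 4 points in the Minnesota score".

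Sidedness is not stated again for any of the three.

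**The concern.** A crossover with 338 completers and a known SD of within-patient differences has a small standard error, SD/√338. The printed LVEDV limit is about twice what that standard error implies, and an SF-36 power of 92% is far too low for a margin of 8.5. This suggests that the SDs of differences were entered as per-group SDs in a parallel-group calculation, contrary to the declared method.

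These two sections are where the article says what the secondary endpoints can resolve. A reader would take 7.4 ml as the edge of detectability for LVEDV and 8.5 SF-36 points as adequately powered with little to spare. Neither describes the within-patient comparison that the Statistics section plans to analyse with linear mixed effects models. A statistician who follows the declared method cannot reproduce the figures.

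**Working it through.** **Inputs, all from the protocol article.** SD of differences 23.8 ml (LVEDV) and 26 (SF-36); SD 15 of unstated type (Minnesota); 5% level; 90% power for the limits; 338 patients, with 177 + 177 in the bracket. One-sided testing is carried over from the primary endpoint, and two-sided results are given alongside.

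**Formulas.** The normal approximations below can be checked by hand. Results marked *nct* are the exact noncentral-t values.

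- Paired: SE = SD/√n.
- Two groups of m: SE = SD × √(2/m).
- Limit at 90% power = (1.645 + 1.282) × SE; power at margin d = Φ(d/SE − 1.645).

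**Step 1: find what reproduces the printed figures.** Two groups of 177, one-sided 5%, with √(2/177) = 0.1063:

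- LVEDV: SE = 23.8 × 0.1063 = 2.53; limit = 2.927 × 2.53 = 7.40 (nct 7.42). Printed: 7.4.
- SF-36: SE = 26 × 0.1063 = 2.76; 8.5/2.76 − 1.645 = 1.43; power 92.4% (nct 92.3%). Printed: 92%.

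Two groups of 169 (338 in total) give 7.59 ml and 91.2%, which do not round to the printed values. Two-sided testing with 177 per arm gives 8.22 ml and 86.6%. Peak VO2 behaves in the same way: SD 2.4, margin 0.75, one-sided 5% and 90% power give 177 per arm as two groups, but 90 patients in total if paired.

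**Step 2: apply the declared method.** Paired, n = 338, √338 = 18.385:

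- LVEDV: SE = 23.8/18.385 = 1.295; limit = 3.79 (nct 3.80; two-sided 4.21). Power at 7.4 ml exceeds 99.9%.
- SF-36: SE = 26/18.385 = 1.414; 8.5/1.414 − 1.645 = 4.37; power exceeds 99.9%. The 90% limit is 4.14 (nct 4.15; two-sided 4.60).

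**Step 3: Minnesota, under each reading of the SD of 15.**

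| Method (one-sided 5% unless stated) | Limit at 90% power | Power at 4 points |
|---|---|---|
| Paired 338, 15 is the SD of differences | 2.39 | 99.9% |
| Two groups of 177, SD 15 | 4.68 | 80.5% |
| Paired 338, 15 is a single-occasion SD with independent visits (15 × √2 = 21.2) | 3.38 | 97% |
| As the row above, two-sided | 3.75 | 93% |

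No row gives 90% power at 4 points.

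**Step 4: check the statements that are not in question.** Even in the two-group calculation with 177 per arm, power is above 99.9% at 12.5 ml LVEDV and at 12 Minnesota points. Both statements of more than 99% are therefore true under either method.

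**Step 5: sensitivity to the unresolved N.** With 354 pairs instead of 338, the one-sided limits are 3.71 ml (LVEDV), 4.05 points (SF-36), and 2.34 or 3.31 points (Minnesota, by type of SD).

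**The case against.** **The Minnesota figure may not be an arithmetic error.** A reader might infer that all three figures are proven wrong. For Minnesota the article does not support that. If 15 is a single-occasion SD and the test is two-sided, the paired limit of 3.75 rounds to 4 whole points. The fit is loose, since power at exactly 4 would be 93% and not 90%, but the type of SD is open and its source cannot be consulted here. What stands is that the figure cannot be reproduced as described.

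**The margins do not rest on these figures.** A reader might infer that the secondary margins, and the conclusions drawn from them, are compromised. The 12.5 ml margin is half of a 25 ml effect of resynchronization, and 8.5 is half of an improvement of about 17. Neither derives from 7.4 ml or 92%. The conclusions will come from the mixed models fitted to observed data. This objection stands in full.

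**The error is conservative.** It is tempting to infer a loss of power, but under the declared paired design the LVEDV and SF-36 figures understate precision. Enrolment is set by peak VO2. This also stands, and it limits the point to a correction of stated properties.

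**The figures could come from a paired calculation with fewer patients.** Since 2/177 = 1/88.5, about 90 pairs would give nearly the same numbers (7.40 ml; 92.4%). The article prints no such N and attributes the figures to 338, so this does not rescue the text. The printed 177 per arm makes the two-group origin the natural explanation.

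**This is a consequence of the primary calculation.** The root is shared with the conflict between 338 and 177 + 177, and the two should be handled together. Correcting that total alone would still leave 7.4 ml and 92% wrong for a paired test.

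**Conclusion.** The point holds for LVEDV and SF-36. For 338 pairs at one-sided 5%, the 90%-power LVEDV limit is 3.8 ml where the article prints 7.4 ml, a ratio of about 1.95. SF-36 power at 8.5 is above 99.9% where it prints 92%, and the corresponding 90% limit is 4.1 points. Two-sided testing moves the limits only to 4.2 ml and 4.6 points, so unstated sidedness does not explain the gap. For Minnesota, the conclusion is that 90% power at 4 points is not reproduced with an SD of 15, and that the article leaves the meaning of that SD open.

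These results take the article's SDs at face value, as SDs of differences for LVEDV and SF-36. They assume that those SDs apply to assessments six months apart, which the article does not establish; a larger SD would raise the limits in proportion. The statements of more than 99% power, the margins of 12.5 ml and 8.5, and the enrolment target of 400 are not affected by this point.

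**What to change.** 1. In Sample size calculations, reconcile 338 with 177 + 177, and state which N the secondary figures use.
2. Restate the LVEDV and SF-36 figures by the declared paired method for that N, and give the sidedness. For 338 pairs at one-sided 5%: LVEDV 3.8 ml at 90% power; SF-36 above 99.9% power at 8.5, and 90% power at 4.1 points. For two-sided 5% the 90% limits are 4.2 ml and 4.6 points.
3. Say whether the Minnesota SD of 15 is that of within-patient differences or of a single score, and restate the limit to match. For 338 pairs, one-sided, it is 2.4 points in the first case and about 3.4 in the second if visits are independent.

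The cost is a wording correction in the protocol and in any analysis plan that repeats the figures. Margins, endpoints, enrolment and analysis need no change on this account.

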### Quality of life and NT-pro BNP

For SF-36, the standard deviation of the difference of scores has previously been reported to be 26 [17]. Previous studies of CRT have reported improvements of ~17. With 338 patients we have 92% power to detect a margin of equivalence of 8.5 at a significance level of 5%. For the Minnesota questionnaire, mild improvements in QoL are represented by a change of 12 with a typical standard deviation of 15 [48]. With 338 patients we would be able to easily detect a mild improvement of this magnitude (>99% power) and have 90% power to detect an equivalence limit of 4 points in the Minnesota score.

For NT-proBNP, CARE-HF reported median reductions of 656 pg/ml in NT-pro BNP (adjusted for change in control group) [10]. The within subject coefficient of variation (σ_w_/mean) in log NT-proBNP levels in people with chronic heart failure over 12 months has been reported to be ~10%, i.e. around 190 pg/ml [57]. Assuming a log normal distribution of NT-proBNP, with 338 patients we will be able to easily detect an equivalence limit of half the clinically reported difference with >99% power at 5% significance level and have 90% power to detect an equivalence limit of 0.062 log units (i.e. a fall in baseline NT-pro BNP from 1900 pg/ml to 1647 pg/ml) at a 5% significance level.

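### NT-proBNP planning treats a 10% CV of log NT-proBNP as 190 pg/ml, and the stated 90% and >99% powers do not follow from that log-scale variability

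*Protocol article*

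**What the plan says.** The section *Quality of life and NT-pro BNP* introduces its variability as "The within subject coefficient of variation (σ_w_/mean"), and continues "in log NT-proBNP levels in people with chronic heart failure over 12 months has been reported to be ~10%, i.e. around 190 pg/ml". It takes 656 pg/ml as the reduction reported after CRT and assumes NT-proBNP is log normal. It then makes two claims for 338 patients. Power exceeds 99% for a limit of half the reported difference, and the trial would "have 90% power to detect an equivalence limit of 0.062 log units", glossed as "i.e. a fall in baseline NT-pro BNP from 1900 pg/ml to 1647 pg/ml) at a 5% significance level".

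The test is set under *Sample size calculations*: "All sample size calculations were based on paired t-tests comparing outcomes for echocardiographic optimization versus haemodynamic optimization". The primary calculation there is a "one sided *t*-test of equivalence in means". The same section gives the number: "On this basis 338 patients (N1 = 177/N2 = 177) are required".

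**The concern.** The sentence on variability joins a log-scale CV and a raw-scale SD as if each restated the other. They are not equivalent in any log base, so a reader cannot tell which SD lies behind the powers. The two powers should follow from the SD, the number of patients and the test, all of which the article states. If they do not, the reported precision for one of the three named secondary outcomes is wrong. Depending on the reading, either the power is overstated or the limit is much wider than the design needs. Anyone who reuses 190 pg/ml or 0.062 carries the error forward.

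**Working it through.** **Inputs** (all from the protocol article)

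- Level 1900 pg/ml, limit 0.062 log units (1900 to 1647), CV about 10%, reported reduction 656 pg/ml: section *Quality of life and NT-pro BNP*.
- Paired t-test, one-sided, 338 patients: section *Sample size calculations*. The NT-proBNP text says 5% without repeating the sidedness, so one-sided 5% is used here and two-sided results are given beside it.

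**Log base.** log10(1900/1647) = 0.0621, so the article works in log10 and its conversion of 0.062 to 1647 pg/ml is right.

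**The conversion**

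- Raw scale: 0.10 × 1900 = 190 pg/ml.
- Log scale: log10(1900) = 3.279, and 0.10 × 3.279 = 0.328 log10 units. 10^0.328 = 2.13, so one SD runs from 1900/2.13 ≈ 893 to 1900 × 2.13 ≈ 4042 pg/ml. The factor is the same in any base.
- A raw CV of 10% under log normality is an SD of √ln(1.01)/ln(10) = 0.0433 log10. The ratio of the two SDs is 0.328/0.0433 ≈ 7.6.

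**Formulas.** The text defines the SD as σ_w, the SD of one measurement within a subject. For a paired difference:

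- SD_diff = √2 × σ_w and SE = SD_diff/√338
- power = Φ(limit/SE − 1.645)
- 90% limit = (1.645 + 1.282) × SE = 2.926 × SE

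**Log reading.** SD_diff = 1.414 × 0.328 = 0.464 and SE = 0.464/18.38 = 0.0252.

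| Quantity | Limit (log10) | Power, one-sided 5% | Power, two-sided 5% | Stated |
|---|---|---|---|---|
| Stated limit | 0.062 | 79% | 69% | 90% |
| Half of 656, fall 1900 to 1572 | 0.082 | 95% | 90% | >99% |
| Half of 656, rise 1900 to 2228 | 0.069 | 86% | 78% | >99% |
| Halved on the log scale, log10(1900/1244)/2 | 0.092 | 97.7% | 95% | >99% |

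The noncentral t distribution changes none of these by more than about 0.3 percentage points. The one-sided 90% limit is 2.926 × 0.0252 = 0.074 log10 (1900 to about 1603). To have 90% power at 0.062 would take (2.926 × 0.464/0.062)² ≈ 479 pairs.

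**Raw reading.** SD_diff = 1.414 × 0.0433 = 0.0613. Power at 0.062, and for half of 656, is essentially 100%. The 90% limit is 2.926 × 0.0613/18.38 = 0.0098 log10 (1900 to about 1858), and 0.062/0.0098 ≈ 6.4.

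**What would reproduce 90% at 0.062**

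- Paired, 338: SD_diff = 0.062 × 18.38/2.926 = 0.39. The readings above give 0.464 and 0.061.
- Two groups of 177: SD = 0.062/(2.926 × √(2/177)) = 0.199. The readings give 0.328 and 0.043.
- σ_w = 0.328 used, without √2, as the SD of the paired difference: 96.6% one-sided and 93.5% two-sided at 0.062.
- σ_w = 0.328 in two groups of 177: 55% at 0.062, and 76% for the fall to 1572.

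None of these routes, with the CV taken as 10%, gives 90%.

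**The case against.** The strongest reply is that 0.062 was computed as some other figures in the article appear to have been, from an SD that is not printed. Two groups of 177, one-sided 5%, 90% power and an SD of 0.20 log10 give a limit of 0.0622. The same formula gives the LVEDV limit of 7.4 ml (7.40), the SF-36 power of 92% (92.4%) and nearly the 0.75 ml/kg/min margin (0.747). It does not give the Minnesota limit (4.67 against 4). With SD 0.20, halving the reported reduction on the log scale gives 99.6% power, which fits the claim of more than 99%. Halving it in pg/ml gives 98.7%.

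This is a plausible account of where 0.062 came from, but it does not make the text right. An SD of 0.20 appears nowhere in the article, it is neither 10% of the log mean nor 190 pg/ml, and a two-group formula contradicts the stated paired test.

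Three further points have force:

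- The CV is approximate. Paired one-sided power at 0.062 is 92% at a CV of 8%, 86% at 9%, 83% at 9.5% and 76% at 10.5%. Reaching 90% needs a CV near 8.4%, which would not normally be quoted as about 10%. A single figure of 79% should still be read with that range.
- On the raw reading the trial has more power than stated, so the shortfall is conditional on the log reading. The cited source is not at hand to settle which applies.
- The endpoint is secondary and does not set the sample size, so the consequence is limited.

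**Conclusion.** The point holds. That 190 pg/ml is not a 10% CV of log NT-proBNP is certain and depends on no assumption about the test. On the log-scale variability as quoted, power is about 79% at 0.062 rather than 90% (76% to 83% for a CV of 10.5% down to 9.5%). For half the reported reduction it is about 95% rather than more than 99%, with a range of 86% to 97.7% depending on direction and on the scale of halving. On the raw reading the claim of more than 99% is true, but the 90% limit is about 0.010, not 0.062.

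These figures assume the stated paired test, one-sided 5%, 338 patients, 1900 pg/ml as the level at which the log mean is taken, and √2 × σ_w as the SD of the difference. The error should be corrected, but it does not touch the primary endpoint or the size of the trial.

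**What to change.** Check the cited source for which variability it reports, then restate the paragraph on one scale, naming the log base (10) and giving the SD of the paired difference.

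- **If the source gives 10% of the log mean:** delete the 190 pg/ml gloss. State an SD of difference of 0.464 log10, about 79% power at 0.062, 90% power at 0.074 (1900 to about 1603 pg/ml), and about 95% power for half the reported reduction. Say that the halving is in pg/ml and the change is a fall.
- **If it gives 10% of the raw value:** remove the word log from the description of the CV. State an SD of difference of 0.061 log10 and restate the 90% limit as about 0.010 log10 (1900 to about 1858 pg/ml). The claim of more than 99% can stay.
- **If another SD was used, such as one near 0.20:** print it with its source, and recompute both powers with the paired test the article declares.

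The cost is wording in the protocol or the SAP. One stated secondary power may become less favourable; recruitment and the primary analysis do not change.

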### Adverse events

All adverse events will be documented. Serious adverse events are defined as those which are not anticipated or not known to be related to the condition being studied or the intervention being used that would result in any of the following outcomes: death, life-threatening condition, unexpected/unplanned in-patient hospitalisation, persistent or significant disability or incapacity, is a congenital anomaly or birth defect.

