### Inclusion and exclusion criteria

Study inclusion and exclusion criteria are shown in Table 1. Patients must have a previous diagnosis of symptomatic chronic heart failure and have been implanted with a biventricular pacemaker or biventricular defibrillator device. The device must have been implanted at least six months prior to enrolment, because cardiac reverse remodelling is known to occur after implantation and one of the secondary outcome measures is left ventricular volumes. We wanted to minimize the potential for any differential effect on remodelling of the two optimization schemes to be interfered with by effects arising from recent implantation of the device.

**Table 1 T1:** Inclusion and exclusion criteria

** *Inclusion criteria* **	** *Exclusion criteria* **
A previous diagnosis of chronic heart failure	Major cardiovascular event within 6 weeks prior to enrolment
Cardiac Resynchronisation Therapy Device (CRT) implanted at least six months prior to enrolment.	Uncontrolled hypertension
A history of symptomatic congestive heart failure (NYHA Class II to IV).	Participation in any other clinical trial which would conflict with this trial
At any time in the past, an ejection fraction <40% or documented moderate to severely impaired systolic dysfunction.	Any condition that will preclude them from walking on a treadmill adequately or participating fully in the study
Stable medical therapy for heart failure	
The patient is willing, able, and committed to participate in the study for the full length of the follow-up.	
>90% biventricular pacing at entry	

Since the primary endpoint is peak VO_2_ measured using a treadmill cardiopulmonary exercise test, ability and willingness to walk on a treadmill is an inclusion criterion.

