### Study conduct and regulatory issues

This study is conducted in compliance with Good Clinical Practice (GCP) guidelines, consistent with the most recent version of the Declaration of Helsinki. The study has been approved by the South West London Research Ethics Committee (3) and site specific assessments were performed for each participating hospital.

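### The serious adverse event definition filters on expectedness and relatedness, so anticipated heart-failure deaths and admissions are documented but not classed as serious

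*Protocol article*

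**What the plan says.** The Adverse events section of the protocol article opens with a broad commitment: "All adverse events will be documented". It then defines the serious subset in a single sentence with two parts. The first part is a filter: serious events are "defined as those which are not anticipated or not known to be related to the condition being studied or the intervention being used". The second part is a list of outcomes, including "death, life-threatening condition, unexpected/unplanned in-patient hospitalisation, persistent or significant disability or incapacity". An event must satisfy both parts to be serious.

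The condition is given under Inclusion and exclusion criteria: "Patients must have a previous diagnosis of symptomatic chronic heart failure and have been implanted with a biventricular pacemaker or biventricular defibrillator device". The Endpoints sections name peak VO2 as primary, and left ventricular remodelling, quality of life and NT-proBNP as secondary. Neither death nor hospital admission is an endpoint.

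**The concern.** Seriousness describes what happened to the patient. Whether the event was expected, and whether it was caused by the disease or by the treatment, are separate questions. The definition merges the three, and the filter works in an unhelpful direction: a known link to heart failure or to the optimization counts against calling an event serious.

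This matters because of what the trial compares. The Background says that biventricular pacing lowers hospitalization and mortality, and that the programmed timings might matter. If the haemodynamic settings were worse for some patients, decompensation, admission or death would be plausible consequences. In patients with symptomatic heart failure these are also the events most readily judged anticipated and disease-related.

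The endpoints do not fill the gap. They are measured at the visit that closes each six-month period, so a patient who dies during a period contributes no peak VO2 for it. A comparison of serious events between the two optimization methods could then leave out events that bear directly on the question.

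**Working it through.** No sample size, power or significance figure is involved. The check is a logical reading of the definition, followed by an attempt to size the effect.

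**Step 1. Write the definition as a rule.** Let A mean that the event was anticipated, R that it is known to be related to the condition or to the intervention, and O that it led to a listed outcome. I take a known link to either the condition or the intervention as enough for R, which is the ordinary sense of the clause.

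- Literal reading: serious = (not A or not R) and O. An event with O is excluded only if A and R both hold.
- Stricter reading (neither anticipated nor known to be related): serious = (not A and not R) and O. An event with O is excluded if A or R holds.

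**Step 2. Apply both readings to every type of event that led to a listed outcome.**

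| Anticipated | Known to be related | Literal reading | Stricter reading | Outcome alone |
|---|---|---|---|---|
| No | No | Serious | Serious | Serious |
| Yes | No | Serious | Not serious | Serious |
| No | Yes | Serious | Not serious | Serious |
| Yes | Yes | Not serious | Not serious | Serious |

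The readings disagree on the two middle rows, so the wording is ambiguous. They agree on the last row.

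**Step 3. Place heart-failure events in the table.** A death or admission from heart failure in this population is related to the condition, so R holds. The sample size section makes allowance for mortality over 12 months, so at trial level deaths are anticipated. Where an individual death or admission is also judged anticipated, it falls in the last row and is not serious on either reading. Where it is judged unanticipated, it falls in the third row and is serious on the literal reading only.

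**Step 4. Try to size it.** The sample size section gives 10% to 15% for mortality and dropout over 12 months, and "the target enrolment is 400 patients".

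- 0.10 × 400 = 40
- 0.15 × 400 = 60

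These 40 to 60 patients are deaths and dropouts together, and the split is not given. The figure does not count admissions. It is therefore neither an estimate of misclassified events nor an upper limit on them.

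**The case against.** The strongest reply is that nothing is lost. Every adverse event is documented, so an anticipated heart-failure death stays in the record and loses only a label. A reader might infer that the definition removes such events from the trial's data. The documents do not support that, and they do not say that safety will be compared on serious events alone. This part of the reply stands and limits the point to classification.

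Second, the literal wording is narrower than it first looks. A reader might infer that any event related to heart failure or to the device is excluded. On the literal reading a related but unanticipated event still qualifies, and the hospitalisation criterion itself speaks of unexpected or unplanned admissions. This also stands. It does not help events that are both anticipated and related, which fail on either reading.

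Third, the Endpoints section argues that worse optimization should appear in the physiological markers, and these are measured whatever the safety wording says. That is fair for patients who attend, and it is why the non-inferiority conclusion on peak VO2 is untouched. It does not cover patients who die before the visit, and it does not count admissions.

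Fourth, an article condenses the full protocol, and safety procedures are often left there. That would answer a complaint about missing detail. Here the article states a definition, and the definition is faulty as stated.

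A reader might also set the definition against the statement "This study is conducted in compliance with Good Clinical Practice (GCP) guidelines" and infer a breach. The article does not reproduce the guidance, so that argument cannot be made from the documents, and the point does not need it.

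**Conclusion.** The point holds as a fault in the stated definition. Seriousness is made to depend on expectedness and relatedness, and events that are both anticipated and known to be related are not classed as serious on either reading of the clause. The stricter reading also excludes events that are only one of the two. Anticipated heart-failure deaths and admissions are in the excluded group, are plausible harms of poorer settings, and are counted by no endpoint.

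The size is unknown. It depends on how many deaths and unplanned admissions occur and how many of them are judged anticipated, and the article gives neither. To say that most such events would be misclassified, or that 40 to 60 would be, goes beyond the documents.

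The conclusion rests on two assumptions: that a known link to either the condition or the intervention satisfies the relatedness part, and that at least some heart-failure deaths or admissions would be judged anticipated. The primary efficacy inference is not affected.

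**What to change.** Define a serious adverse event by the listed outcomes alone, regardless of expectedness or relatedness. For consistency, the hospitalisation criterion should rest on the admission being unplanned, because the word unexpected would bring the filter back. Record expectedness and relatedness as two separate attributes of each event. Classify the deaths and unplanned hospitalisations already documented by the optimization in force when they occurred, so that the two methods can be compared on them.

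The cost is a one-paragraph amendment, a small change to the case report form, and slightly more events to classify as serious. Because all adverse events are documented, past events can be reclassified from existing records. Sample size, endpoints and treatment stay as they are.
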